### Blinding

Knowledge of the participant’s KAM change is required to ensure that the study sample consists entirely of those who experience a reduction in KAMs with at least one insole type. We will randomize patients to either the KAM-R or control group prior to knowing the KAM results and prior to any data collection. After collecting biomechanical data, KAM results will be assessed to verify that the participant experienced a KAM reduction in at least one wedged insole type. As described previously, in cases where the participant does not experience a KAM reduction with either insole, they will be excluded from the main study. Thus our knowledge of KAM changes will not affect our initial randomization, and only be used as a verification tool. Although researchers will be aware of each participant’s study group following randomization (in order to assign the participants in the KAM-R group an insole to take home), the researchers will be blinded during future survey data collection and data analysis as identifying information will be stripped by an independent researcher and replaced with unique patient ID numbers and numerical values for group allocation. Those involved in statistical analysis will be blinded to the group allocation and outcomes during data analysis. All KAM-R participants will be aware as to which condition they have been assigned, based on knowing that they have received an insole. All control condition participants will be aware that they have not received an insole at baseline, but will receive an insole at 3 months. Thus, the study will not be blinded at baseline data collection; however, follow-up data collection and data analysis will be blinded to the researchers.

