### Randomization

Following the baseline laboratory and survey testing, participants will be randomized into one of two study arms: (1) a KAM-reduction experimental group (KAM-R), or (2) a waitlist control group. In the KAM-R group, participants will be given either a medial or lateral wedge insole (whichever insole reduces KAMs more for each individual participant) to put inside their own shoe and use for 3 months. In the waitlist control group, participants will be asked to continue using their own shoes for a period of 3 months, and following this will be provided with access to a wedged insole (whichever reduces KAMs more based on baseline data collection).

Participants will be randomized using a multi-block-randomization procedure into either the KAM-R or waitlist control group. Specifically, a separate block sequence will be used for males and females to ensure an even sex distribution across groups. A block size of 6 will be used for each, and the sequence will be determined from a random number generator.

The one exception to this block randomization procedure is that if neither wedged insole produces a KAM reduction, the participant will be excluded from the main study altogether. This scenario will not be common, as most people do experience a large change in KAMs with one of the two wedged insole types, but this strategy will ensure that all participants in the KAM-R and waitlist control groups are all biomechanically suitable for a wedged insole intervention. Thus, neither group will contain biomechanical non-responders to wedged insoles.

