#### Within group analyses

All data will be analyzed on an intention to treat basis. Changes from baseline to 3 months will be assessed within groups for ordinal data (UCLA score) using Wilcoxon Signed Rank test (α = 0.05). KOOS subsection scores and PASE scores will be compared between baseline and at 3 months using paired-samples t-tests (α = 0.05). KAMs, KAM impulse, varus thrust, and footwear comfort will be compared between the neutral shoe and assigned wedged insole condition at baseline for the KAM-R group using paired-samples t-tests (α = 0.05). All tests will be two-tailed, except in the case of KAMs and KAM impulse, where one-tailed tests will be used. The reason for this is that KAM reduction is strictly controlled in this study and so KAM and KAM impulse reductions are the only possible outcome.

A multivariable linear regression (α = 0.05) will also be conducted on the KAM-R group to evaluate whether KAM reduction, KAM impulse, varus thrust and footwear comfort can predict change in pain over 3 months. Covariates tested in these four models will include adiposity and Kellgren-Lawrence grade.

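### The Randomization and Blinding sections place randomisation at incompatible times, and the Blinding order removes randomised patients despite the stated intention-to-treat analysis

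*Protocol article*

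**What the plan says.** All of the following comes from the protocol article.

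- **Randomization:** "Following the baseline laboratory and survey testing, participants will be randomized into one of two study arms". The same section adds, as an exception to the block procedure, that "if neither wedged insole produces a KAM reduction, the participant will be excluded from the main study altogether".
- **Blinding:** "We will randomize patients to either the KAM-R or control group prior to knowing the KAM results and prior to any data collection". The check comes next: "After collecting biomechanical data, KAM results will be assessed to verify that the participant experienced a KAM reduction in at least one wedged insole type". Then "in cases where the participant does not experience a KAM reduction with either insole, they will be excluded from the main study".
- **Blinding, on who knows the arm:** researchers know each participant's group once randomisation has happened, and "Thus, the study will not be blinded at baseline data collection". Follow-up data collection and analysis are to be blinded.
- **Biomechanics (Laboratory testing protocol):** gait testing in three footwear conditions, the DXA scan and the surveys all take place at the baseline visit.
- **Within group analyses:** "All data will be analyzed on an intention to treat basis".
- **Sample size calculation:** 20 per group, 40 in total, raised to at least 46 for 15% dropout.

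**The concern.** The two sections describe different trials at the point that matters most for a randomised comparison. If the Randomization order is followed, and the KAM result is read before the assignment is opened, a patient whose KAM falls with neither insole is a screen failure and never enters the randomised set. If the Blinding order is followed, the same patient has already been allocated and is then taken out.

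The second order has three consequences:

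- The analysed set is a subset of those randomised, which is not what intention to treat means.
- An eligibility decision is made at a time when the arm may be known to those making it.
- Patients are lost from a total that was inflated only for dropout.

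The Blinding section defends its order by saying that knowledge of KAM cannot then influence the randomisation. That protects the assignment. It does not protect the later decision to keep or remove a patient.

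**Working it through.** **1. Can both orders hold?** The three statements side by side:

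| Section | Sequence |
|---|---|
| Randomization | baseline laboratory and survey testing → randomise |
| Blinding | randomise → collect data → assess KAM → exclude non-responders |
| Biomechanics | KAM testing, DXA and surveys are all part of the baseline visit |

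Baseline testing includes the KAM test, so randomisation cannot come both after it and before any data collection. The Blinding text cannot be read as merely preparing the list in advance. It speaks of randomising patients, and it builds on that order: the KAM result serves only as a later verification, and baseline is declared unblinded.

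**2. Does the Blinding order conflict with intention to treat?** Allocation comes first, the KAM assessment second, exclusion from the main study third. The excluded patients were randomised, so an analysis without them is at best modified intention to treat. The article does not call it that.

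**3. The plan's own sample size.** Inputs from the Sample size calculation section: difference 13.4 points, SD 15, power 80%, significance level 0.05 (two-sided for KOOS under Statistical analysis). The formula that reproduces the stated figure is the two-sample one:

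n per group = 2 × [SD × (z₀.₉₇₅ + z₀.₈₀) / difference]² = 2 × [15 × (1.960 + 0.842) / 13.4]² = 19.67, rounded up to 20.

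The 46 equals 40 × 1.15. Dividing by the retained share instead gives 40 / 0.85 = 47.06, or 48 when rounded up. This small difference is not the point here. What matters is that the 46 contains dropout and nothing else.

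**4. What exclusions would do to the 46.** The article gives no non-responder rate and says only that the situation will be uncommon. The share e below is therefore an assumption.

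- Removed = 46e
- Completers = 46 × (1 − e) × 0.85
- Number to randomise for 40 completers = 40 / [0.85 × (1 − e)], rounded up

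| Assumed e | Removed | Completers | Randomise for 40 completers | Power, formula of step 3 |
|---|---|---|---|---|
| 0% | 0 | 39.1 | 48 | 79.8% |
| 2% | 0.9 | 38.3 | 49 | 79.0% |
| 5% | 2.3 | 37.1 | 50 | 77.7% |
| 10% | 4.6 | 35.2 | 53 | 75.5% |
| 15% | 6.9 | 33.2 | 56 | 73.1% |

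The power column shows scale only. It uses the two-sample formula because that reproduces the 20, whereas the article describes its calculation as within-group and calls the between-group tests exploratory.

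**5. Under the other order.** If the KAM result is confirmed before assignment, e among randomised patients is zero by construction and the conflict in step 2 disappears.

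**The case against.** The case for leaving the plan alone is a serious one. The exclusion rule is numeric, identical in both arms, and rests on measurements made in all three footwear conditions for every participant before any take-home use. Applied objectively, it costs patients but need not bias the comparison. The sample size and main tests are within-group, and the between-group comparisons are declared exploratory. The exclusion rate is unknown, so the loss may be small.

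Much of this stands, and it rules out several stronger readings that a reader might infer:

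- **That staff who know the arm choose which gait trials count.** The article does not say who accepts trials or decides exclusions. Gait speed is checked by photocells and contact by the other foot is a plain fact; only landing near the plate centre leaves latitude. The text supports that researchers may know the arm, not that they select trials by it.
- **That baseline KOOS pain is shifted by knowledge of the arm.** The experimental group is said to know its arm from receiving an insole, and the insole cannot be chosen until the KAM results are analysed. Nothing states that participants know their arm when they complete the baseline survey, so a shift of any given size has no documented mechanism.
- **That the resulting bias is certain or beyond repair.** Keeping everyone randomised in the analysis would restore intention to treat. Making the check blind to arm would remove the main route to selective exclusion.
- **That the fixed block size is part of the same fault.** The statement "A block size of 6 will be used for each, and the sequence will be determined from a random number generator" raises a separate, secondary matter of preference. The article does not describe who has access to the sequence, and may leave that to the full protocol.

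The objection does not remove the contradiction itself or the mismatch with intention to treat. The exploratory label limits the consequence but does not cancel it: the between-group comparison is the only randomised one, and the hypothesis at the end of the Background is stated between groups.

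**Conclusion.** The point holds as a contradiction in the text with a definite consequence for the analysis set. The two randomisation times cannot both be followed. Under the Blinding order, randomised patients are removed after allocation, so the analysed set is not the promised intention-to-treat set.

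Bias is possible because researchers may know the arm when the check is made. It is not certain, because the rule is common to both arms and uses a baseline measurement.

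The loss is about 2 to 7 of 46 patients if 5% to 15% are non-responders, leaving about 37 to 33 completers against the 40 planned. Those figures rest on an assumed exclusion rate and on the plan's 15% dropout. The contradiction and the intention-to-treat conflict rest on no assumption. The two sections should be reconciled before the plan is relied on.

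**What to change.** Use one order in both sections:

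1. Complete the baseline surveys and the three-condition gait test.
2. Process the gait data and confirm a KAM reduction with at least one insole.
3. Log eligibility.
4. Reveal the next assignment from a concealed sequence.

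In the Blinding section, delete the sentence that places randomisation before the KAM results and before data collection, together with the text that treats the KAM check as a later verification. Reword the statement that baseline is unblinded, since baseline would then precede allocation. In the Randomization section, say explicitly that the KAM result is assessed before assignment, and count non-responders as pre-randomisation screen failures. The Blinding section's own aim, that KAM knowledge should not steer assignment, is met by concealment.

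If allocation must come first, have the KAM check made blind to arm, name the set modified intention to treat, report exclusions by arm, and add an allowance for them to the 46.

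The cost is a wording change and gait processing before assignment, which may delay handing over the insole. The KAM result is needed to choose the insole in any case. Varying the block size within sex is optional.

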#### Adherence

At baseline, participants will be asked to refrain from utilizing any alternate therapies during the study period (aside from anti-inflammatory or acetaminophen medication), and asked to utilize the prescribed footwear condition as frequently as possible during the day. While not an exclusion criteria of this study, participants will be asked to try and always use the insole in the same shoe tested at baseline. We will conduct a survey at 1 month, 2 months and 3 months follow-up to evaluate participant adherence to the intervention, which will include recall of the number of hours per day using the assigned insole over the past week, recall of the number of times in the past week a different shoe from baseline was used with the insole, and recall of the number of times alternate allowable therapies were used, such as targeted exercise for OA or anti-inflammatory and acetaminophen medications. Use of therapies that are considered as exclusion criteria (i.e. viscosupplementation, knee braces, narcotic pain medication), will also be recorded.

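### The blinding claimed for follow-up data collection and analysis does not hold as written, because the adherence survey asks about insole use that only one arm can have

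*Protocol article*

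**What the plan says.** The Blinding section of the protocol article accepts that "researchers will be aware of each participant’s study group following randomization", because someone has to hand out the insoles. It then claims blinding from that point on: "follow-up data collection and data analysis will be blinded to the researchers". The mechanism is that "identifying information will be stripped by an independent researcher and replaced with unique patient ID numbers and numerical values for group allocation". For the analysts the claim goes further: "Those involved in statistical analysis will be blinded to the group allocation and outcomes during data analysis". The same section says openly that participants in both arms know whether they have an insole.

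The Adherence section describes a survey at 1, 2 and 3 months. Two of its items concern the insole itself: "recall of the number of hours per day using the assigned insole over the past week" and "recall of the number of times in the past week a different shoe from baseline was used with the insole". The KOOS and Physical activity sections place the KOOS, PASE and UCLA at the same three follow-up points. The Randomization section defines the comparator: "In the waitlist control group, participants will be asked to continue using their own shoes for a period of 3 months", with access to a wedge only afterwards.

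The adherence survey is listed under Secondary outcome measures, and adherence is among the variables in the between-group comparison. Under Within group analyses, the baseline comparison of own shoe with assigned insole is for the KAM-R group only, and so is a regression that "will also be conducted on the KAM-R group to evaluate whether KAM reduction" and the other listed measures predict change in pain.

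**The concern.** Coding protects allocation only if nothing else in the record gives the arm away. Here two routine follow-up questions have a meaningful answer in one arm only. Whoever takes or reads the survey can tell the arm from the answer, and whoever opens the coded file can tell which code is which.

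The primary outcome is self-reported KOOS pain in a trial without a placebo control. Masking the staff and analysts is meant to limit uneven prompting, uneven effort to retain participants, and data-dependent choices in the analysis. If that masking is not in place, a report that repeats the Blinding section would tell readers that a safeguard operated when it did not, and they would misjudge the risk of bias.

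**Working it through.** The plan gives no figure for this point, so there is none to reproduce. The check sets the sections side by side, followed by one illustration.

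**Data collection**

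1. Blinding at follow-up is said to come from stripped identifiers and coded groups (Blinding).
2. The survey at 1, 2 and 3 months asks about hours of insole use and about wearing the insole in another shoe (Adherence).
3. Controls wear their own shoes without an insole for those 3 months (Randomization). Their answer to both items is zero or not applicable.
4. Any positive answer therefore identifies a KAM-R participant. Removing the name does not alter the answer.
5. The article does not say that these items are withheld from the people who collect or process the KOOS.

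**Analysis**

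1. Adherence is a secondary outcome (Secondary outcome measures) and a variable to be compared between arms (Between group analyses). The latter section places that comparison at baseline, when no insole has yet been worn. The survey starts at 1 month, so the adherence data that will exist are follow-up data.
2. Once they are in the analysis file, the code with positive insole hours is KAM-R and the other is control.
3. Blinding analysts to outcomes contradicts their task, since the outcomes are what they analyse.

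**Illustration of how easily the code is broken**

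Inputs: 20 analysed participants per group (Sample size calculation), and an assumed probability p that a KAM-R participant reports any insole use. The article gives no value for p, so a range is shown. Answers are taken as independent. The code stays hidden only if all 20 report no use, with probability (1 − p)^20. The expected number identified directly by a positive answer at one contact is 20 × p.

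| Assumed p | (1 − p)^20 | 20 × p |
|---|---|---|
| 0.1 | 0.12 | 2 |
| 0.5 | about 1 × 10⁻⁶ | 10 |
| 0.8 | about 1 × 10⁻¹⁴ | 16 |
| 0.95 | about 1 × 10⁻²⁶ | 19 |

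Participants are asked to wear the insole as often as they can, so the low end of the range is unlikely. At p of 0.5 or more, the code is almost certain to be readable from the adherence field.

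**The case against.** The strongest reply is that the article does not describe the logistics. It gives shared time points for the KOOS and the adherence survey, but not who administers them, in what order, or whether on one form. An independent researcher already stands between the data and the team and might also remove fields that reveal the arm. A condensed article may leave such detail out. This stands in part: the text does not prove that a given member of staff will see both instruments together. But the article states blinding as a fact and names its mechanism, and that mechanism does not deal with the insole items.

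A reader might also infer four stronger points that the documents do not support.

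- **That the wedge type reveals the arm.** Every participant is tested at baseline in own shoe, lateral wedge and medial wedge (Biomechanics). Controls also have a best wedge defined from baseline data for later use (Randomization). A field for the best wedge can be filled in both arms.
- **That the KAM-R-only analyses cannot be run without the key.** Baseline gait, body composition and KOOS data are collected in both arms, so tests and regressions on these can be run for each code and labelled afterwards. The article is less explicit about whether comfort is rated for the wedges in both arms. The label is needed for reporting, not for the computation in general.
- **That researcher blinding is the only protection.** The article also fixes the tests, the significance level and the contrast from baseline to 3 months, which limits analytic freedom.
- **That the article hides the lack of participant blinding.** It states this plainly.

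**Conclusion.** The point holds for the procedure as written. The article claims that follow-up collection and analysis are blinded, while two adherence items asked at each of the three follow-up points can apply to only one arm and are not kept from those to be blinded. The claim that analysts are blinded to outcomes fails on its own terms.

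This rests on two assumptions: that KAM-R participants report at least some insole use, and that no unstated step separates the adherence data from the KOOS data and the analysts. It does not follow that blinding is unattainable here. Separate forms and staged release would preserve a real part of it.

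The size of any bias in KOOS pain cannot be derived from the article and is probably limited. Participants report the score knowing their arm, and masking researchers would not remove that influence. The sample size and the other stated figures are unaffected. What is at stake is the accuracy of a stated safeguard and a cheap opportunity to make it partly true.

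**What to change.** 1. Have participants complete the KOOS, PASE and UCLA before any adherence question, on forms separate from it.
2. Send the adherence items only to the independent researcher already provided for in the Blinding section.
3. Give the analyst a coded file without adherence data. Complete and lock the KOOS, PASE and UCLA comparisons on that file, then release the adherence data and the group key.
4. Report the KAM-R-only analyses listed under Within group analyses after that release.
5. Reword the Blinding section so that the claim covers only those coded comparisons, and delete the words that extend analyst blinding to outcomes. The statements that participants know their arm can stay as they are.

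The cost is one separate form, a fixed order of analysis, and a small delay before the adherence and KAM-R-only results are available. No additional role is needed.

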### Primary outcome measures

The primary outcome measure in this study will be the KOOS pain score (0–100 points). This measure will allow us to identify the overall treatment effect of the wedged insole intervention over the 3-month follow-up period.

### Secondary outcome measures

Secondary outcome measures include the remaining four KOOS subsection scores (symptoms, function (daily living), function (sport & recreation activities), quality of life; 0–100 points each), PASE (0-400+ points) and UCLA (0–10 points) physical activity scores, peak KAM (Nm), KAM impulse (Nms), varus thrust (mm), adiposity (%), footwear comfort (0–100 mm) and the general intervention adherence survey. In addition, we will use Kellgren-Lawrence grade (grade 1–3) in secondary analyses.

